### Abortion of the study

After including 50 patients in each block, statistical analysis searching for side effects will be done. In case of major complications of EVT, or significant differences between groups, the study will be aborted.

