### Design

A prospective randomized multicenter clinical superiority trial is performed with a balanced randomization. Before the inclusion of the first participant, the trial was evaluated by the Ethics Committee of Rostock University (ID: A 2019–0203). Then, the trial was registered at DRKS (DRKS00023436). It has been accredited by Onkocert of the German Society of Cancer (ST-D483).

During the course and additional centers joining the study, there were positive statements of the following ethics committees: Medical Association of Saxony, Thuringia, Westfalen-Lippe, Bavaria, Baden-Württemberg, and of the Universities of Wuppertal and Düsseldorf.

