### Sample size and statistical analysis

The sample size was calculated with G-Power 3.1. The study will have 60% power to detect a difference of 10%, at a one-sided alpha significance level of 5%, assuming an anastomosis leakage rate of 10%–15%.

Altogether, 362 patients have to be analyzed.

Statistical analysis will be performed using Statistical Package for Social Science (SPSS) version 23.0. All data are regularly transferred from the documentation forms to the database. Statistical analysis will be done using Pearson's *χ*^2^ test (Fisher's exact test).

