## Limited results

Until November 11, 2022, 73 patients have been randomized in the study. Twelve patients had to be excluded for one the following reasons: withdrawal of consent before the operation or intraoperative change of treatment (no anastomosis or no protective stoma).

Results are available for 47 patients. So far, there have been four cases of AL in the control group and two in the EVT group without EVT-related complications.

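### The interim stopping rule names no endpoint, direction or boundary; if it covers leakage, the stated one-sided 5% becomes about 8.7% with Pearson's test or 5–6% with Fisher's

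*Protocol article*

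**What the plan says.** The section on abortion of the study sets one analysis: "After including 50 patients in each block, statistical analysis searching for side effects will be done". The next sentence gives the consequence: "In case of major complications of EVT, or significant differences between groups, the study will be aborted". The two triggers are joined by *or*, so the second stands apart from complications of the sponge treatment. Stopping is stated as mandatory.

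The section on sample size and statistical analysis sets a single error rate, "at a one-sided alpha significance level of 5" per cent, and a single total: "Altogether, 362 patients have to be analyzed". It names Pearson's chi-square test with Fisher's exact test in brackets, and does not mention an interim adjustment. The primary endpoint, in the section on surgery and EVT, is the anastomotic leakage rate.

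**The concern.** A rule that ends the trial on any significant between-group difference gives the primary endpoint a second chance to reach significance, unless the rule excludes that endpoint or sets a stricter threshold. This rule does neither. The error rate quoted for the trial would then be wrong.

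A stop at 100 patients would also rest on a handful of leaks. Only large observed differences can reach significance at that size, so the reported benefit would be too large on average.

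This is more than detail left to a fuller document. The article fixes a mandatory stopping criterion and words it so that a reader cannot tell whether a difference in leakage triggers it.

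**Working it through.** **Inputs**
- Total 362, from the sample size section. The Design section says the trial is "performed with a balanced randomization", so 181 per arm.
- One-sided 5%, critical z = 1.645.
- Leakage rate from the sample size section: "assuming an anastomosis leakage rate of 10%–15" per cent. Both ends and the midpoint are used as null rates.
- Interim at 50 per arm, 100 patients in total. **Assumption:** block means arm.
- **Assumption:** leakage is tested at both looks at the nominal level.

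The stated power does not enter. The normal approximation uses only the fraction 100/362.

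**1. The stated 5%, final test only.** Pearson's statistic is z = (x/n − y/n) / √(2p̄(1−p̄)/n), where x and y are the leaks in the control and sponge arms and p̄ is the pooled rate. Exact binomial enumeration at 181 per arm gives 4.86%, 4.93% and 5.00% at null rates of 10%, 12.5% and 15%. So the stated figure holds when there is no interim test.

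**2. Two looks, normal approximation.** The correlation between the two statistics is √(100/362) = 0.526. Overall error = 1 − Φ₂(1.645, 1.645; 0.526) = 0.087.

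**3. Two looks, exact.** Enumerate all outcomes at 50 per arm, stop if significant for benefit, otherwise add 131 per arm and test again.

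| Null rate | Pearson, final only | Pearson, both looks | Fisher, final only | Fisher, both looks |
|---|---|---|---|---|
| 10% | 4.86% | 8.79% | 3.46% | 5.30% |
| 12.5% | 4.93% | 8.59% | 3.61% | 5.65% |
| 15% | 5.00% | 8.56% | 3.74% | 5.84% |

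**4. Other readings**
- Interim two-sided 5%, final one-sided 5%, Pearson, counting only false claims of benefit: 6.6–6.9%.
- Look repeated every 50 per arm (50, 100, 150, 181), one-sided: 11.4%.
- Block meaning 50 patients in total, one early look: 9.1%.
- Safety-only look with no test of leakage for benefit: no increase.

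**5. How few leaks would stop the trial at 50 per arm**
- 3 versus 0: z = 0.06 / √(2 × 0.03 × 0.97 / 50) = 1.76. One-sided p is 0.039 with Pearson and 0.121 with Fisher.
- 4 versus 0: z = 0.08 / √(2 × 0.04 × 0.96 / 50) = 2.04. One-sided p is 0.021 with Pearson and 0.059 with Fisher.

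The choice of test, which the article leaves open for this look, decides whether such a result stops the trial.

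**6. Exaggeration after an early stop for benefit, one-sided 5% (exact)**

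| True rates | Test | Stops at interim | Mean observed difference among stops |
|---|---|---|---|
| 15% v 10% (5 points) | Pearson | 18.2% | 14.4 points |
| 15% v 10% (5 points) | Fisher | 11.9% | 15.9 points |
| 15% v 5% (10 points) | Pearson | 52.9% | 14.3 points |
| 15% v 5% (10 points) | Fisher | 38.8% | 15.8 points |

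**7. With a strict interim boundary.** Interim one-sided p<0.001 and final one-sided 5%, Pearson: 4.88%, 4.95% and 5.02% at the three null rates (normal approximation 5.04%).

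**The case against.** The strongest defence is that the look is introduced as a search for side effects and sits next to major complications of the sponge. The between-group differences may then be only those found in that search. A stop for harm produces no false claim of benefit, so the efficacy error rate would stay where it is. This reading is possible and cannot be excluded. It does not settle the matter: the stopping sentence carries no such limit, and leakage is itself the main harm of the operation, so a comparison of side effects could easily include it.

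The second defence is the test. With so few events at 50 per arm many analysts would use Fisher's test, and the overall error is then only 5.3–5.8%. That stands, and it means about 9% is not a lower limit. The interim still lifts Fisher's error from 3.5–3.7% to above the stated 5%, and the exaggeration after an early stop is no smaller.

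Three stronger readings are not supported:
- A reader might infer that the trial's error rate is certainly 9% or more. That needs leakage to be tested, Pearson's test to be used, and, to go clearly above 9%, repeated looks. The article states no series of looks.
- A reader might compound the chance of a false stop over several outcomes. The article does not list the outcomes compared at the look, so no such figure can be given. A false abort is also not a false claim of benefit.
- A reader might take the leak counts by arm in the limited results ("So far, there have been four cases of AL in the control group and two in the EVT group", from 47 patients) as an unplanned efficacy test. No test is reported and no denominators per arm are given. Releasing counts by arm during recruitment is unwise, but it is a side remark here.

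**Conclusion.** The point holds in conditional form. The article fixes a mandatory stopping rule that, as worded, covers the primary endpoint and has no boundary, while the error rate is stated as if there were a single test.

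If leakage is tested under that rule at a nominal one-sided 5%, the overall error is about 8.7% with Pearson's test and 5.3–5.8% with Fisher's. It is 6.6–6.9% for false claims of benefit with a two-sided interim, and about 11% if the look repeats every 50 per arm. With true rates of 15% and 10%, an early stop for benefit would show roughly three times the true difference.

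These figures assume that block means arm and that leakage is among the differences tested. If the look is for safety only, there is no inflation and the defect is one of wording. By the limited results, 73 patients had been randomised, fewer than the 100 assumed for the look, so at that date the wording could still be settled before it.

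**What to change.** State the timing as 50 analysed patients per arm (100 in total), if that is what block means. Replace the between-group criterion with one of two rules:

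- **(a) Harm only.** The interim reviews harm, and leakage is not tested for benefit. The final test keeps its one-sided 5%.
- **(b) Benefit with a boundary.** Leakage stops the trial for benefit only at one-sided p<0.001, and the final test keeps its nominal one-sided 5%. Overall error is 4.9–5.0% with Pearson's test.

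In either case keep the harm review as a separate item, and say which of the two named tests is used at each analysis. As a side measure, release no further outcome counts by arm before the final analysis.

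The cost is one protocol sentence and no extra patients. Under (b) the chance of stopping early for benefit falls: by the same enumeration with Pearson's test, from 18.2% to 0.5% if the truth is 15% v 10%, and from 52.9% to 4.3% if it is 15% v 5%. Under (a) there is no early stop for benefit.

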## Limited results

Until November 11, 2022, 73 patients have been randomized in the study. Twelve patients had to be excluded for one the following reasons: withdrawal of consent before the operation or intraoperative change of treatment (no anastomosis or no protective stoma).

Results are available for 47 patients. So far, there have been four cases of AL in the control group and two in the EVT group without EVT-related complications.

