## Discussion

If the hypothesis proves to be true, anastomosis leakage could be reduced significantly by placing a vacuum sponge over the anastomosis for 5 days. This would be a very easy method to reduce AL, probably without side effects.

Any hospital interested in participating in the SEVTAR study is encouraged to contact the corresponding author.

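### Leak counts by arm were published with results for 47 of 362 patients, while recruitment is open and no masking is described; further by-arm release should stop

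*Protocol article*

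**What the plan says.** All of this is in the protocol article.

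- **Limited results:** "Until November 11, 2022, 73 patients have been randomized in the study". Twelve were excluded. "Results are available for 47 patients", and then: "So far, there have been four cases of AL in the control group and two in the EVT group without EVT-related complications". The number of patients per arm is not given.
- **Sample size and statistical analysis:** "Altogether, 362 patients have to be analyzed". The design difference is 10%.
- **Abortion of the study:** "After including 50 patients in each block, statistical analysis searching for side effects will be done". The study may also be aborted if the groups differ significantly. No other interim look is described.
- **Discussion:** "Any hospital interested in participating in the SEVTAR study is encouraged to contact the corresponding author".
- **Participants and recruitment; Randomization; Surgery and EVT:** a surgeon at the centre recruits. The allocation is sent back to the hospital, and only the treatment group receives a sponge. Other care follows local practice. At 30 days a questionnaire is completed by telephone or at a visit. Indicators such as pain, fever, pus or blood oblige the hospital to look for a leak. The list of indicators is open-ended.

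**The concern.** Leak rate is the primary end point, and it is shown by arm to the people who run the rest of the trial. The article never states who is masked. However, the hospital receives the allocation, the operating team places the sponge, and no sham is described, so it is reasonable to infer that treating staff know the arm. In that setting, not knowing how the comparison is developing is an important remaining protection.

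A centre that has read four against two may select patients differently, manage controls differently, or be quicker to recognise a leak symptom in one arm than in the other. None of this would be visible in the data, and the final test could not correct for it. The counts rest on six events and say almost nothing about the sponge, so conduct could be steered by chance.

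**Working it through.** **1. Timing and exposure** (inputs from Limited results and from Sample size and statistical analysis; 362 is taken as stated)

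- Share of the target with results: 47/362 = 13.0%.
- Randomised and not excluded: 73 − 12 = 61.
- Retained but awaiting results: 61 − 47 = 14.
- Not yet recruited on 11 November 2022: 362 − 61 = 301, and 301/362 = 83%.

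The last line is a ceiling. Patients recruited between that date and publication could not have been influenced by the article, and the text does not give the publication date. It also assumes that the 47 and the 14 all count towards the 362.

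**2. Position relative to the planned look**

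The article does not define block. If it means arm, the look needs 100 included patients, and 73 had been randomised, so it was not yet due. If it means a run of 50 patients, the 61 retained had passed that number, but results for 50 were not yet available. On neither reading are the published counts presented as that look.

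**3. What the counts can show** (arm sizes assumed, total 47)

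Fisher's exact test on 4 control leaks against 2 EVT leaks:

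| Control/EVT | Two-sided p |
|---|---|
| 20/27 | 0.38 |
| 22/25 | 0.40 |
| 23/24 | 0.42 |
| 24/23 | 0.67 |
| 25/22 | 0.67 |
| 27/20 | 1.0 |

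At 23/24 the rates are 4/23 = 17% (exact 95% interval 5 to 39%) and 2/24 = 8% (1 to 27%). The difference is 9 points in favour of the sponge, with a Newcombe 95% interval from about −11 to +30 points.

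With six leaks, equal arms and no true effect, the probability of a split of 4:2 or more uneven in either direction is 2 × (15 + 6 + 1)/64 = 0.69.

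The result is what chance would often produce, yet it reads as a halving and lies close to the 10% design difference.

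**4. Sensitivity of the final test to unequal detection** (illustration only; every input below is assumed except the one-sided 5% level)

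The simulation uses equal true leak rates of 10 to 15%, 181 patients per arm and a one-sided 5% chi-square test. The first 24 per arm are unaffected, so 2 × 157 = 314 are affected. That is practically everyone without a result (362 − 47 = 315), hence an extreme case.

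| EVT-arm leaks missed after release | False-positive rate |
|---|---|
| 0% | about 5% |
| 10% | 8 to 10% |
| 20% | 14 to 18% |

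This shows that modest differences in detection would matter. It is not evidence that any occurred.

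**5. Could a before/after-publication split repair it?**

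Take the 47 patients at 23/24 as the early stratum. The standard error of its log odds ratio is √(1/4 + 1/19 + 1/2 + 1/22) = √0.848 = 0.92. Even with unlimited later data, the ratio of odds ratios would have to reach exp(1.96 × 0.92), about 6, to be significant at two-sided 5%. The split would also be confounded with centres joining over time.

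**The case against.** The release has happened and cannot be recalled. No test was reported on the counts, and no further by-arm report is announced. A condensed article commonly leaves to the full protocol who sees interim data, so the absence of a described committee or firewall is no fault. All of this stands. The point rests only on what the article prints, and the remedy looks forward.

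Several stronger readings are tempting, and the text does not support them:

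- **That 87% of the sample (315 patients) will be recruited under this influence.** The 315 are patients without results. Fourteen of them were already recruited, so the ceiling for later recruitment is 301.
- **That surgeons may choose whether to investigate a symptom.** Surgery and EVT requires a search once an indicator is present. Discretion remains in recognising and reporting an indicator from an open-ended list, and in how the search is done.
- **That withdrawals show control patients already leaving.** Withdrawal of consent is pooled with intraoperative change of treatment, is not given by arm, and precedes the article.
- **That hiding the accumulating comparison is the only masking left.** Telephone follow-up is allowed, so a masked caller or masked assessment of leaks is also conceivable.

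A case for openness towards prospective centres can be made. The pooled count and the recruitment figures serve it without showing a direction, and the absence of EVT-related complications can be reported without leaks by arm.

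**Conclusion.** The point holds as a risk that is cheap to limit. The primary end point was released by arm at 13% of the target, outside the one look the article describes, to centres that recruit, treat and recognise leak symptoms with knowledge of the allocation. Up to 301 of 362 patients (83%) could be affected at recruitment or later, and symptom reporting could be affected in some of the 14 awaiting results. For every arm split examined the counts are compatible with chance.

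The conclusion rests on the inference that treating staff are unmasked and on assumed arm sizes. A reader might infer that the trial is already biased. The documents do not show that, and nothing here invalidates the patients enrolled so far.

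**What to change.** - In this and any further report, give only the pooled figure: 6 leaks in 47 patients.
- State that outcomes by arm will not be released to sites, new centres or the public until the last 30-day check is complete.
- State that the analysis under Abortion of the study returns only continue or stop to the centres.
- If the primary comparison is later split by randomisation before and after publication, label it descriptive. The early stratum is too small to detect or remove bias.

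The cost is a short amendment and no extra patients. If nobody outside the centres yet runs the interim analysis, someone has to be named; the article does not say. The downside is that by-arm results can no longer be used to attract centres.

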**FLOWCHART 1 F1:**
[figure not shown]
The flowchart shows the process from recruiting the patient to filing the documentation sheets.

**FLOWCHART 2 F2:**
[figure not shown]
The flowchart shows the SEVTAR study.

## Discussion

If the hypothesis proves to be true, anastomosis leakage could be reduced significantly by placing a vacuum sponge over the anastomosis for 5 days. This would be a very easy method to reduce AL, probably without side effects.

Any hospital interested in participating in the SEVTAR study is encouraged to contact the corresponding author.
